## Aims and Scopes

A major focus of our research is to gain insights into the environmentally triggered plasticity of the regulome in the nasal and bronchial epithelium—a portal of entry for many potential triggers of asthma and the epigenome of these cells as a probable molecular interface between the environment and genome interpretation. One of our main research projects is the analyses of non-coding RNA molecules (small interfering RNA, microRNA, medium, and large RNAs). To give an overview, Figure 1 summarizes the effects of extracellular trigger factors on the nasal and bronchial epithelium. The biogenesis of small interfering, medium, and large RNAs, which we also focus during our investigations, are not presented here. In detail, small non-coding RNA molecules will be holistically analyzed in the biomaterials (e.g., serum samples, nasal epithelial cells) of the cohort, and the interaction to the naso-/broncho-epithelium will be enlightened to figure their role as targets in experimental cell culture models. Our laboratory has previously established a special miR-specific isolation protocol in cooperation with the colleagues from Paris/France, which allows us to analyze all miRs in one sample through the next-generation sequencing (NGS) method. Weil et al. (2017) previously described in detail each methodological step for the microRNA characterization from biomaterials (21). In addition, we have established an adenovirus-vector system for functional analyses of the selected non-coding RNA molecules. The exposure of risk factors and the influence on exacerbation and course will be analyzed in *in vitro* models. Subjects will not undergo any interventions or allergic exposure. To implement this idea, we established an organotypic three-dimensional (3D) cell culture model of primary human nasal and bronchial epithelial cells from numerous healthy and affected study participants where these vectors can be validated. Furthermore, we will analyze these targets-of-interest in mouse models where gene therapeutic techniques, e.g., CRISPR/Cas will be used to knock-down the molecule-of-interest to present the affected signaling pathway. Here, we will also use *Dermatophagoides pteronyssinus* extracts to mimic a somewhat exacerbation model *ex vivo*. Furthermore, the effect of *D. pteronyssinus* on virus infection and on cell integrity will be tested. This project is still under publication. Here, subject-derived biomaterials are essential to perform *in vivo*-like experiments. Our major focus will be the exploitation of potential biomarkers for diagnostic use, which may possibly open new sources for therapeutic regimens in the near future.

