Then, cytokine and chemokine analyses in different biomaterials, e.g., serum, plasma, and induced sputum, will show whether an acute exacerbation is associated with specific “cytokiome” levels and whether their release can be used as potential laboratory exacerbation parameter in clinical routine. The additional biomaterials, particularly sera/plasma and cells obtained from the study cohort, may support the idea of translational research to establish biomarkers for early diagnosis of exacerbation and rapid treatment to reduce morbidity and mortality. The experimental results will be compared by correlation analyses with the clinical item parameters obtained from the questionnaires. The listed network partners (including life scientists and physicians) are clinically and experimentally experts in their area, and the methods are appropriated to implement these research questions into praxis. Most of the described projects have been done or will be performed soon.

In summary, the main focus of our clinical and experimental work is to detect new phenotypes and endotypes, evaluate developed biomarkers and to identify new biomarkers, to uncover the functions of individual cells during an exacerbation, and to decipher the characterization of the microbiome and its role during exacerbation.

Due to the significance of this extraordinary study design and population and the currently performing analyses on the biomaterials with the emphasis on different clinical and molecular levels will present comprehensive insights into the molecular “barcodes of asthma,” which might contribute to improving our understanding of relevant common and individual pathomechanisms, and as such may serve as a highly relevant example for implementation the idea “from patient to bench and from the bench back to the children's hospital” to provide a potential clinical and therapeutic translation.

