## Methods and Analysis

To counteract to this concern, we have built a clinically prospective, multicentered, observational exacerbation cohort to provide deeper insights. Starting in winter 2018, we have now established a pediatric exacerbation network in Germany. The study recruitment is currently ongoing, up to date having already recruited 176 study subjects having chronic bronchitis/wheezing episodes (age group <6 years, *n* = 62), children and adolescents with bronchial asthma (age group >6 years, *n* = 55) presenting recurrent asthma attacks, as well as healthy children, adolescents, and adults (*n* = 59). Currently, our biomaterial collection comprises approximately 2,500 specimens, including sera, plasma, cells, swabs, and sputum.

The study cohort comprises two diseased groups (acute exacerbated wheezers and asthmatics) and healthy children and adults. The subjects will not undergo any interventional/allergic provocations.

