The inclusion criteria for subjects with asthma are based on international recommendations, including lung function parameters (25), a gestational age over 37 weeks with an inconspicuous peripartal/postnatal period, and presenting an acute asthmatic attack at study enrollment. The definition of subjects with a wheeze is based on previously published data (26–29), including a history of at least two obstructive bronchitis episodes and acute wheezing at study enrollment, as well as an inconspicuous peripartal/postnatal period. Patients (chronic bronchitis and asthmatics) suffering from acute wheezing, respiratory illness, dyspnea, chest tightness, etc. (acute respiratory symptoms) were classified as “exacerbators.” The recruitment of wheezers is clinically and scientifically promising because underlying mechanisms of whether wheezers will develop chronic asthma are not sufficiently understood. Epigenetic signatures/environmental factors are likely to play important roles in disease development and persistence of symptoms (30, 31). We aim to analyze similarities between wheezers and asthmatics to make the diagnosis at the early stages of the disease and to discover potential biomarkers for the clinical routine. Moreover, subjects with no chronic diseases or chronic medication and an inconspicuous neonatal period were classified as healthy controls (age range: 3 months to 65 years of age). The healthy pediatric controls will be age- and sex-matched with diseased children (preschool asthmatics/wheezers and asthmatics). The recruitment of healthy adults will be helpful for correlation analyses of age-dependencies. In the future, we are also planning to include adult asthmatics. This is currently in consideration with the entire study members.

All individuals will be observed on the basis of two follow-up (FU) visits to recognize how the “active” and “non-active” phases are presented and differ, respectively (Figure 2).

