All analyzed biomaterials and data involving human participants are in accordance with ethical standards and with the Helsinki declaration (1964) and its later amendments or comparable ethical standards. Ethical approval and later amendment approvals are obtained by the Ethics Committees of Witten/Herdecke University and Ärztekammer Nordrhein, and the study is registered at the German Clinical Trials Register (DRKS). All experiments, including the data extraction and analyses, were and will be obtained pseudonymously. The obtained subject-relevant information and biomaterials were and will be separately coded with study-relevant numbers and codes. All subject-relevant data and experimental results will be filled in a database to perform correlation analyses. With this coding strategy, except the (deputy) study head, nobody may follow retrospectively to patient-sensitive information. All biomaterials were processed according to established internal standard operating procedures and were stored at −80°C or in liquid nitrogen until experimental use. The study recruitment is still ongoing, and the current subject and biomaterial numbers allow first pilot experiments and statistical analyses. The description of the collected data will be done on the basis of statistical parameters. Insofar as the distribution of the data enables, the comparison of the two groups will be carried out using analyses of variance and typical significance tests. Data will be presented as box plots with medians, interquartile ranges, minimum–maximum values or standard deviation, or standard error of the mean. In addition, the data will be presented and analyzed by heat maps, cluster analyses, point clouds, bar, and column charts. Moreover, sequencing results will be normalized within each group, and normalization methods, e.g., DeSeq2, will be performed as previously described by Anders and Huber (33). In addition, metagenomic and proteomic data will be analyzed by professional biostatisticians within our study network. The raw data will be uploaded on separate repository databases, as stated by the journal's requirements. For the experiments, age- and sex-matched stratification will be done between diseased and healthy groups in which each diseased patient will be compared with the same healthy children based on age and sex.

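### The aim is a diagnostic marker, but the named tests and correlations do not measure how well a marker separates individual children; at 55 to 62 per group an observed AUC near 0.60 is already significant (assumed two-sided alpha 0.05)

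*Protocol article*

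**What the plan says.** Aims and Scopes states the purpose: "Our major focus will be the exploitation of potential biomarkers for diagnostic use". For cytokines and chemokines, the same section asks whether an acute exacerbation goes with particular levels, and then "whether their release can be used as potential laboratory exacerbation parameter in clinical routine". Advantages and Pitfalls adds that clinical applicability can be verified.

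The inferential methods are named in two places. The statistics paragraph at the end of Methods and Analysis says that, where the data's distribution permits, "the comparison of the two groups will be carried out using analyses of variance and typical significance tests". Aims and Scopes adds correlation of the experimental results with the clinical questionnaire items. The statistics paragraph also lists heat maps, cluster analyses, several kinds of plot and DESeq2-type normalisation of sequencing data.

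Methods and Analysis gives recruitment so far: "chronic bronchitis/wheezing episodes (age group <6 years, *n* = 62"; "children and adolescents with bronchial asthma (age group >6 years, *n* = 55"; "as well as healthy children, adolescents, and adults (*n* = 59". The last group was "classified as healthy controls (age range: 3 months to 65 years of age".

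The article states no alpha, effect size, target sample size, discrimination measure or rule for when a marker counts as successful.

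**The concern.** A laboratory parameter for routine care has to classify the individual child. What matters is how far the marker's distributions in the two groups are separated, that is, its sensitivity, specificity and AUC. A significance test asks whether the groups differ at all. Its p-value mixes the size of the difference with the number of subjects, so it can be small while the distributions overlap heavily. A correlation with a questionnaire item measures association, which is also a different quantity.

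So the named methods can answer the first half of the cytokine question (is exacerbation associated with these levels?) but not the second half (can the level serve as a parameter in routine care?). If the second is answered from the first, a marker with little practical sensitivity could be put forward as an exacerbation parameter.

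**Working it through.** **Check on the article's own figures.** 62 + 55 + 59 = 176, which matches the stated total. There is no power calculation or AUC target to reproduce.

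**Inputs.** Group sizes 62, 55 and 59, from Methods and Analysis. Assumed, because the article gives neither: two-sided alpha 0.05, and normal marker values with equal variance.

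**Formulas.**
- Smallest observed standardised difference that is significant: d = t(0.975, n1+n2−2) × √(1/n1 + 1/n2)
- AUC = Φ(d/√2)
- Sensitivity at 90% specificity = Φ(d − 1.2816)

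**Example, 55 v 59.** √(1/55 + 1/59) = 0.1874 and t = 1.981, so d = 0.371. AUC = Φ(0.263) = 0.604. Sensitivity = Φ(−0.910) = 0.181.

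| Contrast | d | AUC | Sensitivity at 90% specificity |
|---|---|---|---|
| 62 v 59 | 0.360 | 0.601 | 17.8% |
| 55 v 59 | 0.371 | 0.604 | 18.1% |
| 62 v 55 | 0.367 | 0.602 | 18.0% |
| 117 v 59 | 0.315 | 0.588 | 16.7% |

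**Rank test instead of t-test.** The Mann-Whitney large-sample boundary is 0.5 + 1.96 × √((n1+n2+1)/(12·n1·n2)). It gives 0.603, 0.607, 0.605 and 0.591 in the same order, so the result does not depend on comparing means. A three-group ANOVA with only the healthy group shifted gives 0.610.

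**Fewer usable controls.** The 59 include adults, and the paediatric number is not given. With 55 asthmatics against an assumed 40, 30 or 20 matched children, the boundary is 0.615, 0.625 or 0.644.

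**Other alpha levels (62 v 59 and 55 v 59).**
- 0.10: AUC 0.584 and 0.587
- 0.01: 0.632 and 0.636
- 0.0005 (Bonferroni, 100 markers): 0.677 and 0.683
- 0.00005 (Bonferroni, 1,000 markers): 0.706 and 0.712

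At the strictest two levels, 55 v 59 gives d = 0.672 and 0.791. Sensitivity at 90% specificity is then Φ(−0.610) = 27% and Φ(−0.491) = 31%.

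**Observed versus true AUC.** These are boundaries for the observed value. With a true AUC of 0.60 (d = √2 × 0.2533 = 0.358), power is 48% to 50% in the three pairwise contrasts and 61% for 117 v 59. A true AUC of about 0.64 gives 80% power pairwise, and about 0.62 for 117 v 59.

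**Correlations.** The smallest significant |r| is t/√(n−2+t²), which is 0.266 at n = 55 and 0.250 at n = 62, or 7.1% and 6.3% of variance.

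**The case against.** The strongest reply is that this is a condensed article on an exploratory cohort. It speaks of pilot experiments and potential markers, does not present its list of methods as complete, and gives the metagenomic and proteomic analysis to biostatisticians. A full analysis plan may contain ROC analysis, and its absence here would not by itself be a finding. That is right as far as it goes. What stands is that the article does name its inferential methods, and those methods target a different quantity from the diagnostic aim that it also states. Confirmation in cell culture, planned in Aims and Scopes, gives biological support but does not measure discrimination.

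A reader might infer that a marker with an AUC of 0.60 would be declared a success. The article does not support this: it gives no alpha and no success rule. Nor would such a marker reliably pass, since a true AUC of 0.60 reaches significance only about half the time in the pairwise contrasts.

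A reader might also infer from "values or standard deviation, or standard error of the mean" that the displays will hide the overlap between children. The same sentence begins with box plots, medians and interquartile ranges, and the next lists point clouds, so the spread can be seen. The choice of error bar is a matter of presentation.

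Finally, one might extend the arithmetic to exacerbation against follow-up in the same child. The article gives neither the number of complete pairs nor a within-child correlation, and Advantages and Pitfalls reports poor motivation to attend follow-up. No figure is offered for that contrast.

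**Conclusion.** The point holds as a mismatch between aim and analysis. Significance tests and correlations cannot show that a marker is diagnostically usable. At the current pairwise sizes, an observed AUC of about 0.60 is enough for p < 0.05.

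The figure rests on an assumed two-sided alpha of 0.05, equal-variance normality (for the AUC and sensitivity conversion) and interim group sizes with recruitment continuing. A matched paediatric contrast or multiplicity correction raises the boundary, within the range shown, to at most about 0.71. Even there, sensitivity at 90% specificity is only about 31%, so the conclusion does not hinge on the choice of alpha. It does not show that the study will mislabel markers, only that the named methods would not reveal it.

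**What to change.** Add to the statistics paragraph of Methods and Analysis: for any marker proposed as a diagnostic or exacerbation parameter, report the AUC and the sensitivity at a fixed specificity (for example 90%), each with a 95% confidence interval. Where a panel or cut-off is selected from the data, cross-validate these estimates. Base the diagnostic conclusion on them, and use significance tests and correlations for screening only.

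The interval makes the limits plain. At 55 v 59, an observed AUC of 0.604 has a Hanley-McNeil 95% interval of about 0.50 to 0.71.

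The cost is a few lines of wording and a little extra analysis of data already collected, with no new samples. The downside is that fewer markers will look successful.

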
**Figure 1 F1:**
[figure not shown]
Respiratory epithelium is a gateway for “biocode” research. Respiratory epithelium is constantly connected to environmental factors. Different trigger factors can lead to epigenetic changes. Gene regulatory molecules, i.e., microRNAs, are small non-coding RNA molecules with a length of 21–23 nt, which regulate gene regulation posttranscriptionally (20). Their role and the role of siRNAs and medium and large RNA molecules as potential biomarkers will be analyzed. Experimental design of ongoing experiments to define biomarkers for clinical and therapeutic implementation. This figure was created with BioRender.com.

Descriptively, observed results derived from human samples will be proven in at least cell culture models to establish their clinical and biological connection and highlight their importance for clinical routine (22–24).

Next, the microbial and fungal role of the airway epithelium in nasal and pharyngeal swabs will be explored to highlight potential preventive strategies. Through the NGS method, we will analyze the 16-S and 18-S rRNA in the nasal and pharyngeal swabs of the entire cohort to analyze the microbiome and fungiome levels of exacerbated subjects. A detailed description of the method is currently in publishing, and the details will be shared upon request. With this methodology, we will be able to observe bacteria or fungi where their cultivation with traditional culturing techniques is not possible. Furthermore, we will also start to collaborate with the asthma study network in Greece to compare here phenotype changes between the two countries.

Another focus will the exploitation of the role of IL-33 on regulatory B cells and memory B cells. Co-culture experiments will highlight this functional connection and the influence of IL-33 *in vitro*.

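### The article says sequencing data are normalized within each group, yet plans tests between groups; followed literally, any between-group depth difference would appear as differential expression or abundance

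*Protocol article*

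**What the plan says.** The statistical paragraph of Methods and Analysis in the protocol article states that "sequencing results will be normalized within each group, and normalization methods, e.g., DeSeq2, will be performed" as set out in a cited methods paper. In the same paragraph, "the comparison of the two groups will be carried out using analyses of variance and typical significance tests". That paragraph also shows what a group is, since "age- and sex-matched stratification will be done between diseased and healthy groups".

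Sequencing is central to the aims. Under Aims and Scopes, the microRNA protocol "allows us to analyze all miRs in one sample through the next-generation sequencing (NGS) method". For the microbiome and fungiome, "we will analyze the 16-S and 18-S rRNA in the nasal and pharyngeal swabs of the entire cohort".

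Nowhere does the article say that size factors are estimated jointly over the samples to be compared, or that a later step puts the groups on a common scale.

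**The concern.** Median-of-ratios size factors are relative quantities. Each sample is compared with a reference built from the samples used in the estimation. If diseased and healthy samples are handled separately, each set has its own reference and its factors centre near 1. Depth differences inside a group are removed; a difference in mean depth between the groups is not. It remains as a shift of nearly the same size in every feature and cannot be told apart from differential expression or abundance.

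Control of the false discovery rate does not protect once the shift is material, because most null features move together and their p-values are no longer uniform. The output at risk is the list of candidate small-RNA or microbial markers separating diseased from healthy children.

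Equal mean depth cannot simply be assumed. Patients are enrolled acutely in the emergency room, whereas controls come mostly from staff members' children and range from 3 months to 65 years of age (Methods and Analysis).

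**Working it through.** **No figure to reproduce.** The article gives no depth, dispersion, power or error rate for the sequencing analysis. The only relevant numbers are the group sizes in Methods and Analysis: 62 wheezers, 55 asthmatics and 59 healthy subjects (62 + 55 + 59 = 176, as stated).

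**Mechanism in one feature.** Suppose the true mean is 100 in both groups and diseased samples are sequenced 1.2 times as deeply.
- Within-group factors average about 1 in each group, so the normalized means are 120 and 100. The apparent log2 fold change is log2(1.2) = 0.26.
- Joint factors, with equal group sizes, are √1.2 = 1.095 and 1/√1.2 = 0.913. The normalized means are 120/1.095 = 109.5 and 100/0.913 = 109.5, so the difference is gone.

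**Null simulation.** No feature truly differs; 55 versus 59 samples; negative-binomial counts; per-sample log-depth SD 0.3; t tests on log2 normalized counts. Setting A has 500 features, dispersion 0.3 and 40 repeats. Setting B has 1000 features, dispersion 0.2 and 20 repeats. Dispersion, log-depth SD and depth ratios are assumptions. BH is the share passing Benjamini–Hochberg at 5%, shown where recorded.

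| Setting | Depth ratio | Within-group: p<0.05 (BH) | Joint: p<0.05 |
|---|---|---|---|
| A | 1.0 | 7.2% | 5.1% |
| A | 1.1 | 15.2% | 4.6% |
| A | 1.25 | 52.3% (37%) | 4.9% |
| A | 1.5 | 92.4% (92%) | 4.9% |
| A | 2.0 | 99.9% | 5.3% |
| B | 1.0 | 8.8% (0.7%) | 4.6% |
| B | 1.1 | 20.2% (5.7%) | 5.2% |
| B | 1.2 | 55.3% (42.4%) | 5.1% |
| B | 1.5 | 98.6% (98.5%) | 5.0% |
| B | 2.0 | 100% (100%) | 5.4% |

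Joint factors gave 0% BH discoveries throughout. In setting B the median spurious log2 fold changes at ratios 1.1, 1.2, 1.5 and 2.0 were 0.13, 0.29, 0.61 and 1.03. The log2 depth ratios are 0.14, 0.26, 0.58 and 1.00, so the shift is the depth ratio itself.

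**Hand check of setting B.** With dispersion 0.2, the log of the gamma component (shape 1/0.2 = 5) has variance 0.221 (the trigamma function at 5), so SD 0.470. The standard error of a group difference is 0.470 × √(1/55 + 1/59) = 0.470 × 0.187 = 0.088. At ratio 1.1, z = ln(1.1)/0.088 = 1.08 and the two-sided rejection probability is about 19%. At 1.2, z = 2.07, giving about 54%. Both agree with the table.

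**Why the rate exceeds 5% at ratio 1.0.** Random depth alone gives the difference in mean log depth an SD of 0.3 × 0.187 = 0.056, a typical chance ratio of e^0.056 = 1.06. With identical depth in every sample, within-group factors gave 4.7%.

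**Other comparisons.** For 62 versus 59 (setting B, ratio 1.2), within-group factors gave 50.0% (BH 34.9%). For an assumed matched subset of 20 versus 20, they gave 24% (BH 5%) at ratio 1.25 and 53% (BH 38%) at 1.5.

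**When the error disappears.** In setting B, a joint size-factor step after the within-group step, or scaling each sample to a fixed total, gave 4.5% to 5.4% at p<0.05 and 0% BH at every ratio.

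**The case against.** The strongest reply is that the sentence is loose. It joins two clauses, and the one naming DESeq2 may describe a further step over all samples, following a cited paper that is not at hand. A joint step, or scaling each sample to a fixed total, would remove the problem. This stands as a limit on certainty. It does not rescue the sentence: the article states neither step, and the paragraph uses the word group for diseased versus healthy. Nor is this detail left to a fuller plan, because the article fixes the scope of normalization and fixes it badly.

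A second reply is that pipelines are described elsewhere. Aims and Scopes refers the microRNA steps to a cited paper and the detailed 16S/18S method to a separate publication. The statistical paragraph gives metagenomic and proteomic data to the network's biostatisticians. So one cannot conclude that every sequencing analysis is affected. The Aims and Scopes text establishes that sequencing is planned; it says nothing about normalization.

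A third reply concerns size. No depth difference is reported, and Advantages and Pitfalls describes standardized sample processing. The 59 controls include adults, whereas the planned comparison uses age- and sex-matched children, so a real comparison would probably be smaller than 55 versus 59 at present. This also stands: the inflation shrinks in smaller subsets but does not vanish.

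A reader might also infer that counts already normalized by group are fed into DESeq2, which expects raw counts. The article does not say so.

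**Conclusion.** The point holds as a fault in a stated rule. Normalizing separately within the groups that are then compared is wrong for that comparison, and the article sets out no step that corrects it.

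The consequence is conditional. It scales with the actual ratio of mean depths, which the documents do not give, and falls to nothing if mean depths are equal. Under the assumed counts at 55 versus 59, false positives at p<0.05 run from about 7–9% with no systematic difference, through about 15–20% at 1.1 and about 50% at 1.2 to 1.25, to over 90% at 1.5, against about 5% with joint factors.

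A reader might go further and infer that the study's biomarker findings are false, or that half or more of them would be. The documents do not support that: they report no depth difference, and actual practice may already be joint.

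**What to change.** Replace the clause on within-group normalization with:

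> Size factors are estimated once across all samples of a given biomaterial and assay that enter a comparison. Raw counts enter the model, with group as a model term and not as a normalization stratum.

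Re-run any pilot result that was normalized separately by group. If practice is already joint, only the sentence changes.

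A longer covariate list (visit, age, sex, sequencing run) is not part of this fix and should not be added by default. The disease groups are split at age 6, so age nearly coincides with group in a wheezer-versus-asthmatic contrast. If samples from several visits are analysed together, the model must account for repeated samples from the same child.

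The cost is one sentence and, where needed, a re-run of existing scripts. No new data are required.
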